| Interventions | 11a | 
Experimental Groups (Intervention):
Participants in the experimental groups will engage in a French kiss, defined as a passionate kiss involving the exchange of salivary fluids through the mutual introduction of tongues into each other's mouths, along with lip contact. Participants will receive instructions to perform this kiss for a duration of 40 seconds. While this duration is arbitrary and will be acknowledged as a limitation in the protocol, no prior studies provide a guideline for the specific duration of this type of kiss.
 
 
○ Setting: The intervention will take place in a private space within the dental clinic of the Universidad Católica de Santiago de Guayaquil. Each cubicle, equipped with a dental chair, will be enclosed with screens to ensure the privacy of participants. After completing the kiss, participants will leave the cubicle to provide an unstimulated saliva sample, which will be analyzed to measure pH.
 
 
Control Group:
Participants in the control group will not kiss but will still be required to bring their partners to ensure comparable conditions. The individual who consumes the acidic beverage will remain in the same cubicle for 40 minutes, providing unstimulated saliva samples every 5 minutes, as is required for the experimental groups. The control participants will remain seated and follow the same sample collection timeline as the intervention groups.
 
Implementation Standards:
 
 
○ The intervention (kissing) will be self-administered by participants. The research team will observe the initiation of the kiss to ensure it begins appropriately and will then start the timer
 
 |

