|  |     | 
for the 40-second duration. Once the timer concludes, participants will be asked to leave the cubicle and provide their saliva sample.
 
 
○ Tools and Equipment: 
 
○ Screens (biombos) to provide privacy.
 
○ Timers or stopwatches to ensure accurate intervention durations and sample collection intervals.
 
○ A calibrated pH meter to measure salivary pH.
 
○ Eppendorf tubes (3ml) for saliva collection, suitable for accommodating the electrode of the pH meter and ensuring accurate measurements.
 
 
 
 
Monitoring and Compliance:
To respect participants' privacy, researchers will not remain present during the kiss. However, they will ensure the proper initiation of the intervention and verify compliance with the protocol. Saliva collection and pH measurement will be monitored closely to ensure adherence to the timeline.
 
Justification of the Intervention:
The kiss was chosen as the intervention due to its widespread and accessible nature. Demonstrating that kissing can act as a protective factor against the reduction of salivary pH—and potentially against dental caries—could contribute positively to preventive strategies for oral health. The study aims to explore the physiological impact of kissing in a controlled and measurable manner.
 
Materials and Equipment Used:
 
 
1. Eppendorf tubes (3ml): These will collect unstimulated saliva and accommodate the pH meter electrode, as only minimal saliva is expected per sample.
 
2. Calibrated pH meter: This device will measure salivary pH with precision.
 
3. Screens (biombos): To ensure the privacy and comfort of participants during the intervention.
 
4. Timers/Stopwatches: To accurately measure the duration of the kiss and sample collection intervals.
 
 
Safety and Monitoring Measures:
The intervention (kissing) is considered a safe and low-risk activity, especially as it will involve habitual partners. The clinic, located within the university, operates with official permits and adheres to national and international standards for disinfection and biosecurity. The privacy provided by screens further enhances participant comfort. In the unlikely event of an unforeseen incident, the university's medical department will be on standby to provide immediate assistance.
 |

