| Outcomes | 12  | 
Primary Outcome:
 
The primary outcome of this study is the time required for salivary pH to return to neutral levels (pH ~7) after the intervention (kissing). The objective is to demonstrate that the act of kissing facilitates a faster restoration of salivary pH compared to the physiological time required in the absence of a kiss.
 
Secondary Outcomes:
 
 
1. The salivary pH level measured at each time interval during the 40-minute observation period.
 
2. Comparison of salivary pH restoration rates between: 
 
o The control group and the two experimental groups.
 
o Experimental group 1 (only one partner consumes the acidic beverage) and experimental group 2 (both partners consume the acidic beverage).
 
 
 
 
Methods of Measurement:
 
A pH meter will be used to measure the hydrogen ion activity in the saliva, reflecting its acidity or basicity. The device employs a Toledo micro combined pH electrode with the following specifications:
 
 
o Measuring range: pH 0 - 14.
 
o Temperature range: 0°C - 80°C.
 
o Shaft dimensions: 60mm length and 3mm diameter.
 
o Glass membrane: U-type with resistance <600M at 25°C.
 
o Reference system: ARGENTHAL with Ag+ ion trap.
 
 
The saliva sample will be unstimulated to avoid pH alterations caused by increased salivary flow. A small sample volume is expected, and the thin electrode design ensures accurate measurement even in reduced quantities.
 
Measurement Timeline:
 
 
1. A baseline saliva sample will be collected before the participants consume the acidic beverage.
 
2. Immediately after ingesting the beverage, a second saliva sample will be collected.
 
3. Participants in the experimental groups will kiss for 40 seconds, while the control group will wait.
 
4. A saliva sample will be collected at 5-minute intervals for the next 40 minutes, resulting in a total of nine post-intervention samples per participant.
 
 
Justification:
 
Measuring salivary pH every 5 minutes is a standard approach in similar studies assessing the dynamics of salivary pH restoration. Additionally, measuring pH immediately after consuming acidic beverages is consistent with other research protocols. Using a pH meter ensures precise and objective measurements, while collecting unstimulated saliva minimizes alterations in pH caused by increased flow rate, enhancing the reliability of the data.
 |

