| Data collection methods                                   | 18a | 
The primary outcome of this study is the time required for salivary pH to return to neutral (pH 7.0) after the kissing intervention, compared to the control group. Baseline data, including the initial pH of unstimulated saliva before the intervention, will also be collected. Secondary outcomes include salivary pH measurements at defined time intervals (e.g., immediately after the intervention and every 5 minutes up to 40 minutes).
 
Data Collection Process:
 
 
○ Participants will expectorate saliva into sterile 3 mL conical Eppendorf tubes at each designated time point.
 
○ A calibrated pH meter will be used to measure the pH of the collected saliva. Calibration will be performed using standard buffer solutions at pH 4.01 and pH 7.01 before each data collection session, ensuring accuracy and reliability of the measurements.
 
○ All pH measurements will be conducted by trained members of the research team, who will follow a standardized protocol to minimize variability and ensure data quality. Duplicate measurements will be taken for 10% of the samples to verify consistency.
 
 
Data Recording:
 
 
○ Measured values will be entered directly into a secure, cloud-based Excel spreadsheet accessible only to authorized members of the research team. This ensures data integrity and confidentiality.
 
 |

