**Figure 1. Schedule of Enrolment, Interventions, and Assessments**

| Study Period                    | Enrolment | Allocation | Post-Allocation | Close-Out |
|----------------------------------------|------------------|-------------------|------------------------|------------------|
| Timepoint                       | Week 1-2         | Week 3            | Week 3-10              | Week 11-12       |
| Enrolment:                      |                  |                   |                        |                  |
| - Eligibility screening                | X                |                   |                        |                  |
| - Informed consent                     | X                |                   |                        |                  |
| - Baseline assessments                 |                  | X                 |                        |                  |
| Interventions:                  |                  |                   |                        |                  |
| - Group Experimental 1                 |                  |                   | X                      |                  |
| - Group Experimental 2                 |                  |                   | X                      |                  |
| - Group Control                        |                  |                   | X                      |                  |
| Assessments:                    |                  |                   |                        |                  |
| - Immediate post-intervention          |                  |                   | X                      |                  |
| - Follow-up (every 5 min up to 40 min) |                  |                   | X                      |                  |
| Data Analysis:                  |                  |                   |                        | X                |

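### Return to neutral is not required to last, and the first sample directly follows the kiss, so a transient post-kiss value could count as recovery in the kissing groups only

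*Protocol*

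**What the plan says.** Protocol item 12 gives the primary outcome as the "time required for salivary pH to return to neutral levels (pH ~7") after the intervention. Item 18a gives it as the "time required for salivary pH to return to neutral (pH 7.0) after the kissing intervention, compared to the control group", and item 20a also uses 7.0. None of the three says whether the first sample at neutral, a confirmed one or a sustained return counts.

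On timing, item 11a says: "Once the timer concludes, participants will be asked to leave the cubicle and provide their saliva sample". Item 12 describes 5-minute sampling over 40 minutes, "resulting in a total of nine post-intervention samples per participant". Figure 1 lists an assessment named "Immediate post-intervention" separately from the 5-minute follow-up. Item 18a gives the times as "immediately after the intervention and every 5 minutes up to 40 minutes", there as an example under the secondary outcomes. Controls do not kiss but follow the same sampling timeline (item 11a).

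On the type of sample, item 11a says: "After completing the kiss, participants will leave the cubicle to provide an unstimulated saliva sample, which will be analyzed to measure pH". Item 12 explains that unstimulated saliva is used "to avoid pH alterations caused by increased salivary flow". Item 16b keeps participants unaware of their group partly because expectation alone may increase salivation.

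**The concern.** The trial asks whether kissing restores salivary pH sooner than the body does unaided. A value that touches neutral just after the kiss and is below it five minutes later does not show that. If the first sample at neutral sets the recovery time, such a participant receives the shortest time possible.

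Only the kissing groups are exposed to this. At time 0 their saliva has just been through a 40-second exchange with a partner, and the controls' saliva has not. By the protocol's own reasoning on flow and expectation, that sample is hard to call unstimulated. At stake is a positive primary result that reflects a momentary difference at one sampling time and not lasting restoration.

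**Working it through.** **1. Is there a time-0 sample?** Samples every 5 minutes over 40 minutes give 40/5 = 8. Item 12 counts nine, and 8 + 1 = 9 if one is taken at time 0. This agrees with item 11a, item 18a and Figure 1. No settling time between kiss and sample is stated.

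**2. What does the outcome wording allow?** With no persistence condition, the plain reading of time to return is the first sample at the target. The approximate 7 and the exact 7.0 can also give different times for the same series.

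**3. Effect on mean recovery time (assumed inputs).** The protocol gives no recovery curve, reading error or size of post-kiss rise. Assume lasting recovery is the same in all three groups, with a recorded mean of 22.5 minutes (normal with mean 20 and SD 8, on the 5-minute grid, limited to 5 to 40 minutes). Suppose a fraction p of kissers is scored 0 because of a transient. The kissers' mean is then (1 − p) × 22.5:
- p = 0.10: 20.3 minutes
- p = 0.20: 18.0 minutes
- p = 0.30: 15.8 minutes

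**4. Effect on the planned test.** Item 20a plans one-way ANOVA, or Kruskal-Wallis if its assumptions fail. Item 14 requires 10 per group before dropout; item 10 and the registration data set give 15 couples per group. Simulating step 3 with both kissing groups affected, the ANOVA rejects at the 5% level as follows, although lasting recovery is identical:

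| Fraction p | 10 per group | 15 per group |
|---|---|---|
| 0 | 5% | 5% |
| 0.10 | 7% | 9% |
| 0.20 | 12% | 19% |
| 0.30 | 24% | 36% |

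Kruskal-Wallis is somewhat lower. Across both tests and both sizes the range for p = 0.10 to 0.30 is roughly 6% to 37%.

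**5. When does the effect vanish, and does a confirmation rule remove it?** Assume pH 6.0 after the drink, a plateau of 7.1 and a time constant of 10 minutes. The true curve crosses 7.0 at 10 × ln(1.1/0.1) = 24.0 minutes. Add a rise at time 0 only. A rise of 0.5 gives 6.5, short of the target. A rise of 1.0 gives exactly 7.0, so about half of the readings reach it. Mean time among those who reach 7.0, first-sample rule:

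| Reading SD | No rise | Rise 0.5 | Rise 1.0 |
|---|---|---|---|
| 0.05 | 26.3 min | 26.3 min | 13.1 min |
| 0.10 | 24.8 min | 24.8 min | 12.4 min |
| 0.18 | 22.3 min | 22.3 min | 11.1 min |

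If two consecutive samples are required, the mean is 25.5 to 27.7 minutes with or without the rise, so the artefact goes. The share with no confirmed return by 40 minutes becomes 5% to 26%, against 0% to 1% under the first-sample rule.

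**6. Noise.** The no-rise column describes a group with no post-kiss effect at all. More noise moves its mean from 26.3 to 22.3 minutes. Controls give the same nine samples, so this shift occurs in every group.

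**The case against.** A reader might infer that the protocol lays down a single-reading rule. It does not. The rule is open, the first sample is only the natural default, and all nine samples are taken, so a stricter rule could still be applied. A confirmation rule is also a detail often left to an SAP. That stands as far as the missing detail goes. It does not remove the conflict within the protocol, which sets two thresholds and calls a post-kiss sample unstimulated against its own reasoning. A rule left open could also be chosen after the data are seen.

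A reader might also infer that noisy readings favour kissing. Step 6 shows why they do not: controls share the timeline.

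The strongest objection is that item 6a names salivary exchange, through dilution and buffering from the partner, as the mechanism under study. A mixed sample at time 0 is then part of the effect and not contamination. This stands. It argues against dropping the time-0 sample from the primary outcome, and leaves only persistence in question.

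Finally, every magnitude rests on assumed values, and the documents do not say whether a kiss would lift pH as far as 7.0. This stands too.

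**Conclusion.** The concern holds in a limited form. The documents establish that return to neutral need not persist, that two thresholds are given, and that the first sample follows the kiss with no settling time while being labelled unstimulated. On the first-sample reading, a transient value at neutral would count as recovery at about 0 minutes in the kissing groups only.

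How much this matters is unknown. It is nil if the rise does not reach 7.0. If 10% to 30% of both kissing groups show a transient at neutral and lasting recovery is otherwise identical, the planned test would be falsely positive in roughly 6% to 37% of trials, against a nominal 5%. The low end is minor and the high end is not. The documents do not support the claim that a false result is likely, only that the outcome as worded does not guard against one. The definition should be settled before data collection.

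**What to change.** - In items 12, 18a and 20a, use one threshold, and define recovery in every group as the first of two consecutive samples at or above it.
- Keep the immediate sample in the series, but do not call it unstimulated. Add a sensitivity analysis that counts recovery from the 5-minute sample onward, since a rise lasting until that sample would still meet the two-sample rule.
- In items 20a and 20b, state that participants without confirmed recovery by 40 minutes stay in the primary analysis as not recovered by 40 minutes, either censored or given the worst rank. Otherwise the complete-case rule in item 20b could remove them.

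**Cost.** No extra samples are needed. The change goes beyond wording, however: an ANOVA of mean recovery times does not accommodate unrecovered participants. Worst ranks suit the Kruskal-Wallis test already named, while censoring needs a time-to-event method. A recovery first seen at 40 minutes cannot be confirmed, recorded times lengthen, and more participants have no confirmed recovery (5% to 26% in the illustration on assumed values).

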| Sample size          | 14 | 
The sample size calculation was conducted using the G*Power statistical software (version 3.1.9.7, Fran Faul, Universität Kiel, Germany). The calculation was based on data obtained from the pilot study titled "Comparison of Salivary pH Changes after Consumption of Two Sweetened Malaysian Local Drinks among Individuals with Low Caries Experience: A Pilot Study". This study measured salivary pH changes after consuming acidic beverages and provided the necessary statistical parameters for sample size estimation.
 
Specifically, the following values from the pilot study were used:
 
 
Control group (mineral water): mean = 7.10, SD = 0.18.
 
Experimental group (local drink): mean = 6.86, SD = 0.18.
 
 
To calculate the effect size (<math>f</math>) for ANOVA, the means and standard deviations were combined using the formula:
 $n = \frac{(2 * (Z\beta + Z\alpha)^2 * \sigma^2)}{\Delta^2}$ 
Given the mean difference (7.10 - 6.86 = 0.24) and pooled SD of 0.18, <math>d=1.33d=1.33d=1.33</math>. Dividing by the square root of the number of groups (<math>k=3</math>), the resulting effect size was <math>f=0.76</math>, which is considered a large effect size.
 
The following input parameters were used in G*Power:
 
 
Effect size (<math>f</math>): 0.76 (large effect size based on observed data).
 
Alpha error probability (<math>\alpha</math>): 0.05.
 
Power (1-<math>\beta</math>): 0.95.
 
Number of groups: 3.
 
 
The output indicated that a total sample size of 30 participants is required to achieve a power of 95%, with 10 participants per group. To account for potential dropouts, an additional 20% will be recruited, resulting in a total of 36 participants (12 per group).
 
This effect size and resulting sample size are justified based on the observed differences in the pilot study, which measured salivary pH using similar methods (pH meter, unstimulated saliva samples in test tubes) and reported statistically significant differences between groups. Using this approach ensures that the sample size is both statistically adequate and logistically feasible for this study.
 |

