| Statistical methods | 20a | 
Analysis of Primary and Secondary Outcomes:
 
The primary outcome, the time required for salivary pH to return to neutral (pH 7.0), will be analyzed using appropriate statistical methods depending on the data distribution. First, tests of normality (e.g., Shapiro-Wilk test) will be conducted to determine if the data follows a normal distribution. If the data meets the assumptions for parametric tests, a one-way ANOVA will be used to compare the mean recovery times across the three groups: control, experimental group 1 (only one partner drinks the acidic beverage), and experimental group 2 (both partners drink the acidic beverage).
 
If the assumptions for ANOVA are not met, the non-parametric Kruskal-Wallis test will be applied to compare the groups. Post-hoc analyses (e.g., Tukey's HSD for ANOVA or pairwise comparisons with Bonferroni correction for Kruskal-Wallis) will be conducted to identify specific group differences.
 
For secondary outcomes, including salivary pH levels at specific time intervals, repeated-measures ANOVA will be used if the data meets parametric assumptions. Otherwise, the Friedman test will be employed to evaluate changes in pH over time within and between groups.
 
Additionally, pairwise comparisons will be performed to assess the differences in mean recovery times between the control group and each experimental group (control vs. experimental 1, and control vs.
                                                                                                                                                                                                                                                                                                                                                                                                                                                                                                                                                                                                                                                                  |

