|                            |     | experimental 2). These comparisons will utilize independent t-tests if parametric assumptions are met or Mann-Whitney U tests if they are not.                                                                                                                                                                                                                                                                                                                                                                                                                                                                                                                                                                                                                                                                                                                                                                                                                                                                                                                                                                                                                                                                                                                                                                                                                                                                                                                                                                                                                                                                                                                                                                                                                                                                                                                                                                                                                                                                                             |

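### Recovery time is compared with unadjusted tests although pre-drink baseline pH is measured in every group, so a small trial gives up precision it could have at almost no cost

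*Protocol*

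**What the plan says.** Protocol item 20a (Statistical methods) makes the primary comparison of recovery time conditional on a normality check. If parametric assumptions hold, "a one-way ANOVA will be used to compare the mean recovery times across the three groups". If not, "the non-parametric Kruskal-Wallis test will be applied to compare the groups". It then adds pairwise contrasts of each kissing group with control: "These comparisons will utilize independent t-tests if parametric assumptions are met or Mann-Whitney U tests if they are not". No covariate is named in item 20a or 20b.

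The measurement timeline in item 12 (Outcomes) has three steps that matter here. First, "A baseline saliva sample will be collected before the participants consume the acidic beverage". Second, "Immediately after ingesting the beverage, a second saliva sample will be collected". Third, "Participants in the experimental groups will kiss for 40 seconds, while the control group will wait". Item 18a (Data collection methods) confirms that "Baseline data, including the initial pH of unstimulated saliva before the intervention, will also be collected". The protocol gives this value no role in the primary comparison.

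The trial is small. Item 14 plans 30 participants, raised to 36 (12 per group). Item 2b gives 45 couples (15 per group).

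**The concern.** The outcome is the time taken to reach a fixed threshold, pH 7.0. A person's resting pH should help predict that time, because it bears on the level from which, and towards which, saliva recovers. A variable that predicts the outcome and is measured before treatment can be put in the model to remove part of the unexplained variation. Item 20a leaves that variation in the error term.

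At stake is the width of the confidence intervals and the power to detect a kissing effect smaller than the one planned for, with 10 to 15 units per group. This is not a detail left open for an analysis plan: the protocol names its tests, and all of them are unadjusted.

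**Working it through.** **1. Inputs.** From item 14: mean difference 7.10 − 6.86 = 0.24, SD 0.18, f = 0.76, alpha 0.05, three groups, 30 participants before dropout and 36 after. From item 2b: 45 couples. R is not in the document and is assumed to be 0, 0.3, 0.5 or 0.7.

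**2. The plan's own figure.** Power of a one-way ANOVA comes from the noncentral F distribution with 2 and N − 3 degrees of freedom and noncentrality N·f². At f = 0.76 and N = 30, noncentrality is 30 × 0.76² = 17.33 and power is 95.0%. The stated sample size is reproduced. At N = 36 power is 98.0%, and at N = 45 it is 99.6%.

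**3. A smaller effect.** Item 14 obtains f by dividing d = 0.24/0.18 = 1.33 by √3. If d = 1.33 is instead the distance between the extreme group means, f depends on where the third mean lies:

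- Third mean halfway: f = 1.33/√6 = 0.54.
- Third mean equal to one of the others: f = 1.33 × √2/3 = 0.63.

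I use 0.54 to illustrate an effect smaller than planned. It is not a forecast, because d describes a pH difference between two drinks and not a difference in recovery time.

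**4. Effect of adjustment.** In a linear ANCOVA, residual variance is multiplied by 1 − R², so f becomes f/√(1 − R²). One covariate leaves N − 4 error degrees of freedom. The variance factors are 0.91, 0.75 and 0.51 at R = 0.3, 0.5 and 0.7. Their inverses, 1.10, 1.33 and 1.96, correspond to 10%, 33% and 96% more participants.

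Example at N = 36, f = 0.544, R = 0.5: adjusted f = 0.544/√0.75 = 0.629, noncentrality = 36 × 0.629² = 14.2, power 90.6%.

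| f | N | Unadjusted | R = 0 | R = 0.3 | R = 0.5 | R = 0.7 |
|---|---|---|---|---|---|---|
| 0.54 | 36 | 80.4% | 80.3% | 84.1% | 90.6% | 98.1% |
| 0.54 | 45 | 89.4% | 89.3% | 92.1% | 96.2% | 99.6% |
| 0.76 | 30 | 95.0% | 94.9% | 96.6% | 98.7% | 99.9% |
| 0.76 | 36 | 98.0% | 98.0% | 98.8% | 99.7% | >99.9% |

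If baseline pH proves useless (R = 0), the price is about 0.1 point of power.

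**5. Which pH value is safe to adjust for.**

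- *Pre-drink baseline.* It is taken before any part of the assigned condition is delivered.
- *Immediate post-drink value.* It precedes the kiss, but that is not sufficient. Items 6b and 8 make who drinks part of the allocation: one partner in experimental group 1, both in group 2. Items 17a and 17b disclose the group on the day of the session without placing disclosure before or after the first two samples. Item 16b itself raises the possibility that knowing the group changes salivation. The post-drink value could therefore be affected by group.

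**The case against.** The strongest case against is that nothing is wrong with the stated tests. Under randomisation the unadjusted comparison is unbiased on average, and its error term already allows for chance differences in starting pH. This stands in full. A reader might infer that a chance imbalance in starting pH could pass for a kissing effect more often than alpha allows; the design does not support that. The loss is one of efficiency.

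A second objection is that the gain rests on assumed correlations and on an f below the protocol's. That stands too. At f = 0.76 there is little left to gain, and at 45 units power is 89% unadjusted even at f = 0.54. The variance factor also holds only for linear ANCOVA. It does not carry over to Kruskal-Wallis or to a time-to-event model, so the table indicates scale only.

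A reader might also infer that both pre-kiss pH values are valid covariates for the primary model. The documents do not support this for the post-drink value, for the reasons in step 5. Adjusting for it could remove part of a real group difference or introduce bias.

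What survives is narrower: the protocol prespecifies only unadjusted tests while holding a suitable covariate, and using it costs almost nothing.

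**Conclusion.** The point holds as a matter of efficiency, limited to pre-drink baseline pH. The planned analysis is valid but discards precision in a trial of 30 to 45 units. If the true effect is near f = 0.54, adjustment is worth about 4, 10 or 18 points of power at N = 36 for R = 0.3, 0.5 or 0.7, and about 3, 7 or 10 points at N = 45. If f = 0.76 is right, the gain is at most about 5 points at N = 30 and 2 at N = 36.

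These figures assume a linear model, normal errors, one covariate and an R that the document does not supply. Some correlation is plausible for a threshold outcome, but its size is unknown. The improvement is worth making, and the trial's validity does not depend on it.

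**What to change.** In item 20a, make the primary analysis one prespecified model of recovery with group and pre-drink baseline pH. ANCOVA is the simple form. Because recovery is read on a 5-minute grid and observation ends at 40 minutes, a time-to-event model suited to such data, with the same covariate, may fit better. Keep the unadjusted test as supportive.

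State in item 12 or 17b when the group is disclosed relative to the first two samples; the baseline sample should come before disclosure. Use immediate post-drink pH only in a sensitivity analysis, unless the protocol can state that this sample is taken before disclosure and cannot be affected by allocation.

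No new data are needed. The statistical cost is one degree of freedom. The administrative cost is the notice to the ethics committee and the registry that item 25 requires for changes to statistical analyses. Item 2b gives the status as not yet recruiting, so on that status the change can be made before any data exist.
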